### Recruitment

Peer advocates will invite individuals from their personal and community networks to participate in the study. Study participants will also be encouraged to refer their friends, relatives, and partners. Given that LGBTIQA + populations are highly networked, this purposive snowball sampling strategy is expected to reach a substantial number of participants. In addition, the peer advocates will use social media platforms to disseminate information. This includes a study-specific Facebook page for each site, where contact details of peer advocates and study sites will be shared. Peer advocates will also distribute study messages through other platforms such as Viber, WhatsApp groups, and online dating sites. All messaging will follow privacy and confidentiality guidelines. Information about the study will be further shared through social and cultural gatherings, as well as via local mass media, particularly community radio (FM stations). Peer advocates will conduct outreach at known gathering places (often referred to as ‘hotspots’) frequented by LGBTIQA + communities to promote the study and encourage participation.

### Randomization and blinding

Participants are randomly assigned to one of the three study arms using simple randomization, with equal allocation ratios (1:1:1 ratio). To ensure impartiality, an independent researcher (not involved in delivering intervention sessions or assessing outcomes) at the central office handles the randomization process. The allocation sequence will be concealed from the peer advocates by ensuring that the peer advocates are informed of the participant’s assignment only after enrolment is completed. The assigned arm will be communicated to the responsible peer advocate by the central study team using the participants’ study code via secure mobile messaging or a telephone call.

Blinding of participants and peer advocates will not be implemented due to the nature of the intervention. The field researchers, who are not involved in delivering the SAATHI intervention, will be responsible for outcome assessments and will not have access to the randomization sequence. Although they may become aware of participants’ allocation during follow-up interviews or by working in the same building as the peer advocates, steps will be taken to minimize detection bias. Measures will include standardized procedures such as structured questionnaires, scripted instructions, neutral delivery of questions, and training of field researchers in assessment procedures. However, the new independent outcome assessors responsible for the final assessment of the primary outcomes will be blinded.

Unblinding of the outcome assessors will be permissible only if knowledge of the assigned intervention is required to ensure participant safety or to enable appropriate clinical management following a serious adverse event. Any request for unblinding will be made by the principal investigator to the researcher responsible for maintaining the allocation list. The allocation will be disclosed only for the individual participant concerned and only to the minimum personnel required. The date, reason, and individuals involved in any unblinding will be documented.

### Data collection methods

The quantitative questionnaires for the randomized controlled trial include screening, baseline, and follow-up instruments. These instruments include demographic questions and standardized validated tools, including the GHQ-12, WHO multi-country questionnaire for violence assessment, WHODAS 2.0, PCL-5, PSYCHLOPS, safety behaviour checklist, MSSS-5, Kristin Neff’s Self-Compassion Scale, and the Modified Collective Self-Esteem Scale. The validated tools were adapted using standard recommended approaches for cross-cultural adaptation of self-reported measures [70]: First, native speakers with relevant expertise translated the tools from English into Nepali, Bhojpuri, and Maithili. Study staff reviewed the translations and resolved discrepancies. Independent bilingual individuals then back translated the instruments into English. The study team compared the back translations with the originals and used the identified differences to refine and finalize the local language instruments. Language experts and community leaders subsequently reviewed the revised instruments to simplify terminology for lay understanding while preserving meaning. The complete questionnaire was pre-tested with 10 field researchers and pilot tested with 28 LGBTIQA + community members to ensure clarity and acceptability. Although the study team had already adapted GHQ-12, WHO multi-country questionnaire for violence assessment, WHO Disability Assessment Schedule 2.0, PCL-5, PSYCHLOPS, and a safety behaviour checklist for vulnerable populations in Nepal [71], we went through all the above steps again to make sure they were also a good fit for the LGBTIQA + community.

During the trial, trained field researchers with public health backgrounds will conduct face-to-face interviews using tablets at enrolment (baseline assessment), at 7 weeks (corresponds to 1 week after sixth session for the intervention groups), 18 weeks, and 12 months after the baseline assessment. Figure 1 illustrates the sequential steps from screening to intervention delivery and follow-up assessments. Interviews will be conducted in Nepali, Bhojpuri, and Maithili based on participant preference. Data collected through REDCap will be synchronized directly with a secure server at the central office. Monitoring and supervision of the field researchers (both scheduled and ad hoc) will take place weekly to bi-weekly during the initial phase and will transition to monthly intervals in later phases to maintain data quality.

To promote participant retention, multiple strategies will be implemented. Contact information, names of alternative contact persons, and preferred times for follow-up calls will be recorded to maintain communication. The central and field study teams will regularly review scheduled visits and follow-up timelines, with the central team providing oversight and coordination as needed. The field team will contact participants to provide timely appointment reminders for follow-up assessments. If a participant misses a follow-up appointment, they will be contacted to reschedule the visit. The study will provide incentives to cover transportation costs and incidental expenses (e.g. mobile data, basic refreshments) as compensation for participants’ time and effort.

#### Training of outcome assessors

The 5-day training of field researchers used a blended learning approach combining lectures, demonstrations, role plays, and hands-on practice with both paper-based and digital tools. It was facilitated by the research team in collaboration with experts with academic backgrounds and applied experience in public health, research methods, and mental health from other organizations. The training covered a range of methodological and ethical topics. Core components included digital data collection using REDCap, participant eligibility screening, administration of standardized assessment tools, referral protocols, and procedures for baseline and follow-up assessments. Given the sensitive nature of the study, field researchers were also trained in foundational helping skills such as respectful and inclusive verbal and non-verbal communication, maintaining confidentiality, rapport building, demonstrating sensitivity to participants’ lived experiences, empathy and exploring and normalizing feelings and assessing psychological harm. The field researchers were shown role play videos illustrating helpful and unhelpful behaviours related to ENACT items 1–7 developed by EQUIP. Role plays and supervised field-testing prepared field researchers to conduct interviews with accuracy and empathy.

### Process evaluation

The process evaluation will include observations and interviews conducted by the central study team. Monitoring visits will assess fidelity to the manual and the quality of counselling sessions. Semi-structured interviews will explore how participants and peer advocates experience the intervention and interpret it within their personal and cultural contexts. Participants will be interviewed about the counselling sessions, the usefulness of the safety planning and empowerment exercises, and the influence of group activities on social support. Peer advocates will be interviewed about their experiences and barriers during intervention delivery. In addition, to complement the quantitative ratings of peer advocates’ competencies, in-depth interviews will be conducted with the peer advocates responsible for delivering the sessions. These interviews will explore their experiences of applying the competencies in real-world settings.

The following research questions will be examined:What do participants and peer advocates experience as facilitators and barriers for change related to the specific components of SAATHI intervention and the social and cultural setting it is conducted within?How participants and peer advocates narrate and give meaning to change processes experienced by participants in relation to the SAATHI intervention (including both positive changes and possible adverse reactions)?How does being a client or peer advocate influence their self-definition in social relationships and narrative constructions of identity?

Data collectors with public health background stationed at central office will conduct in-depth interviews with approximately 20 clients and 20 peer advocates—the exact number will depend upon when saturation in central themes is reached. We will also conduct 3–6 focus group discussions with peer advocates to facilitate collective constructions of meaning based on common experiences. We will conduct only individual interviews with participants to ensure confidentiality and to allow reflection upon how personal background and life context contribute to experiences with the intervention.

The study will also evaluate the peer advocates’ competencies both before and after training using standardized observation tools. This assessment involves structured ratings of behaviours demonstrated during the role plays. Each competency scale will be scored on a four-level scale. Level 1 represents unhelpful or potentially harmful behaviour. Level 2 indicates the absence of skills or only partial demonstration of basic skills. Level 3 reflects the consistent demonstration of all basic helping skills. Level 4 reflects the demonstration of all basic helping skills together with one or more advanced skills. In addition, peer advocates’ practice will be assessed through direct observations of all six counselling sessions for two clients per peer advocate. A standardized checklist developed by EQUIP platform will be used during these observations. Competency will be assessed at three time points: prior to training and immediately post-training using standardized role plays, and during service delivery through direct observation of two counselling sessions, with the most recent observed session used for competency scoring. For each assessment, competency item scores will be averaged to generate mean scores for basic helping scores and PM + specific delivery skills, as well as an overall competency score. Peer advocates will be considered competent for service delivery if they achieve a score of 3 or higher on at least 80% of items and demonstrate no behaviours rated as potentially harmful. As part of the process evaluation, any behaviours rated as potentially harmful during post-training role plays or observed counselling sessions in the field will be shared with the peer advocates to support feedback and skill improvement.

### Data management

All quantitative data will be directly entered into REDCap at the point of collection by field researchers and peer advocates (who will be responsible for entering PSYCHLOPS data only). To minimize data entry errors, the system incorporates built-in validation rules, range checks, branching logic, and predefined legal values. Interim data exports will be encrypted and stored in a secure repository at the central office on a weekly basis. Access to collected data is restricted through role-based permissions and strong password requirements. The study team will conduct regular data quality checks (e.g. missing values, outliers, inconsistencies). Identified errors will be documented in a separate Excel sheet, including site and client codes, and shared with the field teams for resolution.

All qualitative data will be collected using digital audio recorders during in-depth interviews, key informant interviews, and focus group discussions. Informed consent for recording will be obtained prior to each interview. Audio recordings will be transferred to a secure server at the central office. Recordings will be deleted from the recording devices once the transfer is complete. Interviews will be transcribed verbatim in the source language by trained transcribers. Personal identifiers will be removed during transcription. Transcripts will then be translated into English for analysis. A random subset of transcripts will be independently reviewed by another study team member to check transcription accuracy and completeness, and that the original meaning is preserved during translation. Audio recordings will be permanently deleted after verified transcription and completion of quality assurance procedures.

Participants’ confidentiality will be strictly protected through de-identification and secure data storage practices. Quantitative data in REDCap and de-identified qualitative transcripts will be archived in a secure and access-controlled central office repository for 5 years following the date of final publication.

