The peer advocates who deliver the sessions are advised not to conduct more than four sessions per day to prevent emotional burnout. Additionally, they are encouraged to take a 30-min break between sessions to rest. Peer advocates will receive a monthly salary for their role as helpers in the study.

Participants who are allocated to the SAATHI individual plus group (SAATHI-IG) arm will also be invited to attend monthly group meetings (6–10 participants in each group) to strengthen social support. These group meetings will tentatively run for 60 to 90 min. During the sessions, participants can share their experiences with the SAATHI strategies (see Supplementary file 2), discuss the benefits and challenges of applying them in their daily life, and offer peer support. The group sessions aim to help participants maintain strategies that reduce psychological stress.

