To ensure peer advocates could deliver counselling well, we trained them using the Enhancing Assessment of Common Therapeutic factors (ENACT) competency tool from the Ensuring Quality in Psychosocial and Mental Health Care (EQUIP) platform [54, 55]. Core interpersonal skills such as verbal and non-verbal communication, emotional attunement, the ability to explain confidentiality, and risk detection were assessed with standard observation checklists both before and after the sessions that introduced the related content. Specifically, the Nepali version of ENACT items 1–7 from the EQUIP platform was used. For items 8–16 (about PM + Competency) we had them translated and back translated between English and Nepali by subject matter experts and linguistic specialists to ensure semantic and conceptual equivalence.

Our EQUIP-based training also emphasized trauma-informed care, ethical engagement, and cultural responsiveness. We prepared peer advocates to apply these principles in high-risk contexts like supporting participants facing chronic violence and stigma. A key part of this was integrating safety planning and harm reduction strategies specifically designed for ongoing interpersonal or community violence. Peer advocates practised assessing safety risks, developing personalized safety plans appropriate for LGBTIQA + individuals, and navigating local referral systems for protection and support for their clients.

To consolidate learning, each day concluded with structured reflection sessions, in which peer advocates shared experiences and challenges and received feedback on their practice. Role plays based on challenging case vignettes were integrated throughout the training to build confidence and facilitate practical application of the SAATHI intervention strategies.

To prepare peer advocates for the field implementation, all received an orientation on the SAATHI intervention manual. The training also covered essential documentation procedures, such as using adherence checklists, maintaining session registers, entering Psychological Outcome Profiles (PSYCHLOPS) data into the Research Electronic Data Capture (REDCap) tool, and adhering to debriefing protocols. These quality assurance measures are designed to support the fidelity of intervention delivery across implementation sites.

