#### Training of peer advocates in EUC arm

Peer advocates in the control arm completed a structured, 2-day training. Its goal was to ensure the ethical, accurate, and participant-centred delivery of EUC. We equipped advocates with the knowledge and communication skills needed to share mental health and violence prevention information, respond with sensitivity to participants’ needs, and refer clients to mental health care when needed.

The program used a participatory format, blending interactive lectures with case-based discussions, group exercises, and guided demonstrations. It started with orientation sessions that covered the study’s objectives, the role of EUC, and key ethical principles like confidentiality, voluntary participation, and non-coercive communication.

A key part of the training focused on how to clearly explain the scope and limitations of EUC. Facilitators employed pre- and post-test questions to gauge knowledge gains. They also observed role plays performed by the peer advocates and provided feedback to ensure that all peer advocates met the minimum quality standards for dos and don’ts related to ENACT items 1–7, particularly when informing participants about the EUC or administering PSYCHLOPS. Finally, the training introduced procedures for documenting referrals and follow-ups using EUC-specific recording templates.

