The Psychological Outcomes Profile (PSYCHLOPS) [32, 63] of the participants will be assessed using a self-reported measure designed to capture progress from the participants’ perspective by evaluating four questions related to problems, functioning, and well-being. Responses are provided both as free text narratives and on an ordinal six-point scale. Each question is scored from 0 to 5, producing a maximum total score of 20. The tool also includes an item assessing suicidal thoughts. Follow-up assessments will be made at 7 weeks and at 18 weeks after baseline assessments. Follow-up assessments using PSYCHLOPS will also include a question on participants’ current overall perception of change, rated from ‘feeling much better’ to ‘feeling much worse’, compared with their state prior to participating in the SAATHI intervention.

The information about outcome measures is summarized in Tables 1 and 2.

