### Harms

The following harms will be monitored for this trial: increased psychological distress, worsening of existing mental health symptoms, new or intensified suicidal ideation, heightened fear or anxiety, and increased exposure to violence associated with participation in the intervention or research procedures. Studies have shown that there are no observed increases in serious adverse events, such as an increase in suicidal thoughts, associated with PM + when it is delivered by trained and supervised non-specialist helpers [31]. However, PM + will not be offered to high-risk individuals such as those with severe mental disorders or those at heightened risk of suicide, as the PM + is designed to address mild to moderate psychological distress.

Some safety strategies, including disclosure to informal networks or seeking help from formal institutions, may involve risks in certain contexts [64]. These risks can include escalation of violence or retaliation when involving others due to conflicts with the norms of family privacy, particularly when institutional support responses are ineffective. Evidence also indicates that safety planning may be of limited value where access to psychosocial services, housing assistance, and legal protection is constrained, which can leave survivors at continued risk [65]. Ensuring the availability of adequate support services is therefore necessary when promoting safety planning strategies.

As part of the individual counselling and the group sessions, participants will be invited to share and reflect on adversities, as well as explore possible solutions. This process may lead to increased psychological stress or emotional discomfort. Harms will be monitored systematically using tools such as PSYCHLOPS suicidal ideation item during counselling sessions or at follow-up assessments. Any adverse events will be documented using a standardized adverse event reporting form. Any serious events (suicide attempts, hospitalization for mental health reasons, escalation in the risk of violence, or any event that poses substantial danger to the participant) will be reported to the Data and Safety Monitoring Board for review and guidance.

This protocol is designed to safeguard all SAATHI participants. In cases of suicide risk, the study team will provide immediate referral to a mental health specialist, with the participants’ agreement, or link them to local support services in situations of risk of interpersonal violence.

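### The article assigns outcome assessment to non-delivery field researchers but has unblinded, arm-aligned peer advocates administer or enter PSYCHLOPS, a secondary outcome, and does not say who collects the 7- and 18-week scores

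*Protocol article*

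**What the plan says.** Randomization and blinding sets the rule: "The field researchers, who are not involved in delivering the SAATHI intervention, will be responsible for outcome assessments". It makes no exception for any instrument, and it states that peer advocates and participants are not blinded. Data collection methods lists PSYCHLOPS among the trial's questionnaires and has field researchers conduct the interviews at baseline, 7 weeks, 18 weeks and 12 months.

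Three other places give PSYCHLOPS to the advocates:

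- Data management says that quantitative data go into REDCap as they are collected, entered by "field researchers and peer advocates (who will be responsible for entering PSYCHLOPS data only".
- The training section for the SAATHI packages includes "entering Psychological Outcome Profiles (PSYCHLOPS) data into the Research Electronic Data Capture (REDCap) tool" among the documentation tasks taught to advocates.
- The training section for the EUC arm requires minimum standards of conduct, "particularly when informing participants about the EUC or administering PSYCHLOPS".

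PSYCHLOPS is listed in Table 2 as a secondary outcome scored 0 to 20. On timing, the Secondary outcomes text says: "Follow-up assessments will be made at 7 weeks and at 18 weeks after baseline assessments". The follow-up version adds a question on perceived overall change since before SAATHI, and the tool contains an item on suicidal thoughts. Under Harms: "Harms will be monitored systematically using tools such as PSYCHLOPS suicidal ideation item during counselling sessions or at follow-up assessments".

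**The concern.** Two sets of statements assign the same outcome to different staff. This matters because the advocates' role is aligned with arm. They deliver the care ("The peer advocates who deliver the sessions are advised not to conduct more than four sessions per day"), and the control-arm advocates are a separately trained group ("Peer advocates in the control arm completed a structured, 2-day training", against 10 days for the SAATHI packages). Data analysis pools SAATHI-I and SAATHI-IG against EUC at 7 and 18 weeks, which is exactly the split between the two kinds of advocate.

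PSYCHLOPS is self-reported. A participant who gives problem scores, or answers the perceived-change question, to the person who provided the counselling or to a colleague of that person has a reason to answer kindly. A control participant who answers someone whose role was to give information has less reason to. The measures against detection bias in Randomization and blinding are set out for field researchers, and the blinded assessors cover only the final assessment of the primary outcomes. Neither safeguard is stated for PSYCHLOPS scores taken by advocates.

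There is a related point on harms. The suicidal-thoughts item is the only instrument named for harm monitoring. It may be asked in counselling sessions, which EUC does not include, so detection of suicidal ideation could differ by arm.

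**Working it through.** No figure in the plan needs reproducing here. The check compares the sections and then adds an illustration of sensitivity.

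**1. Who collects PSYCHLOPS at 7 and 18 weeks?**

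| Section | What it implies |
|---|---|
| Randomization and blinding | Field researchers, no exception |
| Data collection methods | Field researchers run all interviews; PSYCHLOPS is among the questionnaires |
| Data management | Advocates enter PSYCHLOPS, and only PSYCHLOPS, as it is collected |
| Training, SAATHI packages | Advocates enter PSYCHLOPS in REDCap |
| Training, EUC arm | Advocates administer PSYCHLOPS |

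Entry as the data are collected, together with the EUC wording on administration, points to more than clerical work. One reconciling reading is that advocates record scores in sessions and field researchers record the follow-up scores. It fits the EUC arm poorly, because that arm has no counselling sessions and yet its advocates were prepared to administer the tool. No section states this division.

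**2. What would a collection bias do?** The documents give no value for such a bias, so this is a range under assumption and not an estimate.

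- Inputs from the article: 354 per arm planned, hence 354 EUC and 708 pooled SAATHI; 10% attrition, the maximum assumed in Sample size.
- Evaluable: 354 × 0.9 = 318.6 and 708 × 0.9 = 637.2.
- Standard error of the standardized difference: √(1/318.6 + 1/637.2) = 0.0686.
- Assumed: no true effect, a pure collection bias of b standard deviations between SAATHI and EUC, a two-sided test at 0.05 and the normal approximation.
- False-positive rate = 1 − Φ(1.96 − b/0.0686) + Φ(−1.96 − b/0.0686).

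| b (SD) | False-positive rate |
|---|---|
| 0 | 5.0% |
| 0.05 | 11.3% |
| 0.10 | 30.8% |
| 0.15 | 58.9% |
| 0.20 | 83.0% |

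**3. Schedule of the suicidal-thoughts item.** The last scheduled PSYCHLOPS is at week 18 and follow-up ends at 12 months: 52 − 18 = 34 weeks without that item. Table 3 nevertheless marks adverse-event monitoring at every time point up to 12 months, and Ethics has participants asked about adverse experiences at all follow-up assessments.

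**4. What can still be changed?** Trial status reports 1054 of at least 1062 participants enrolled by 29 December 2025. By that date anyone enrolled before about 10 November 2025 (7 weeks earlier) had passed the first follow-up, and anyone enrolled before about 25 August 2025 (18 weeks earlier) had passed the second. The 12-month interviews run to January 2027.

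**The case against.** The best reply is that collection by advocates at follow-up is inferred. Data management limits what advocates may enter; it does not say that they alone enter PSYCHLOPS. Harms distinguishes counselling sessions from follow-up assessments, and administration by advocates is explicit only for EUC, without a time point. This stands: a reader might conclude that SAATHI participants definitely report their follow-up scores to their own counsellor, and the article does not say so. It leaves the conflict in place, because Randomization and blinding makes no exception and no section states the benign division of work.

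On harms, a reader might infer that suicidality goes unmonitored for 34 weeks, or that SAATHI participants get six extra checks. Neither is supported. The Harms text presents PSYCHLOPS as an example of the tools used and gives no frequency for the session item, and general adverse-event monitoring continues to 12 months. No between-arm test of harms is described either. The absence of a 12-month PSYCHLOPS score is consistent across the article and is a design choice, not an error.

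It is also fair that participants are unblinded, that field researchers may learn the allocation (the article says so), and that a change of interviewer therefore reduces courtesy bias without removing it. Distress at 7 and 18 weeks is also measured by GHQ-12, which advocates do not enter.

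**Conclusion.** The inconsistency is real and should be resolved. As written, a secondary outcome appears to be collected, at least in part, by unblinded delivery staff whose role follows the analysed contrast, against the article's own rule on outcome assessment. If so, the pooled SAATHI versus EUC comparison of PSYCHLOPS at 7 and 18 weeks, including the perceived-change question, is open to bias in favour of SAATHI. That rests on the inference that advocates take the follow-up scores. The size of any bias is unknown, and the table above shows only how sensitive the test would be.

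The reach is limited to PSYCHLOPS and to the comparability of suicidal ideation detected in the different arms. It does not extend to the primary outcomes, which have separate blinded assessors at the final assessment.

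**What to change.** 1. Reconcile Randomization and blinding and Data collection methods with the two training sections and Data management. State that field researchers administer PSYCHLOPS at all remaining 7- and 18-week interviews in every arm, starting on one date for all arms.
2. Record for each score already taken, and for each later one, who collected it. Report a sensitivity analysis by collector. Defining the groups by whether the visit fell due before or after the change keeps the randomized comparison within each.
3. Label advocate-collected scores as process data, or keep them in the outcome with the limitation declared.
4. When arms are compared on harms, report events found at scheduled assessments separately from those found in counselling sessions. State how often the suicidal-thoughts item is asked in sessions, and consider including it in the 12-month interview.

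The cost is a few minutes per interview, a change in data-entry permissions and protocol wording. Because many early follow-ups are already past, collectors will be mixed across calendar time, which is why step 2 is needed. If field researchers have collected all follow-up scores from the start, one clarifying sentence settles the outcome part of the point.
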